### 2.5 Participants timeline

Table 1 provides an overview of the schedule of enrolment, interventions, and assessments.

**Table 1 T1:** Schedule of the study.

	**Study period**						
	**Patients with MDD**						**Healthy volunteers**
	**Inclusion**	**Allocation**	**Post-Allocation**		**Follow-up**		**Experimentation**
**Timepoint (week)**	**-1**	**0**	**1**	**2**	**6**	**14**	**1**
**Inclusion:**							
Eligibility screen	**X**						**X**
Informed consent	**X**						**X**
Demographics	**X**						**X**
Allocation		**X**					**X**
**Interventions:**							
iTBS alone			↔				
iTBS combine with odorants			↔				
**Assessments:**							
MADRS	**X**	**X**		**X**	**X**	**X**	
BDI		**X**		**X**	**X**	**X**	**X**
CTQ		**X**					**X**
Chapman scales		**X**		**X**	**X**	**X**	
SHAPS		**X**		**X**	**X**	**X**	**X**
AES		**X**		**X**			**X**
ETOC/hedonic perception		**X**					**X**
FVT		**X**		**X**			
MRI		**X**		**X**			
Dual-site TMS		**X**		**X**			**X**

iTBS, intermittent Theta Burst Stimulation; MDD, Major Depressive Disorder; MADRS, Montgomery and Asberg Depressive Rating Scale; BDI, Beck Depression Inventory; CTQ, Childhood Trauma Questionnaire; SHAPS, Snaith-Hamilton Pleasure Scale; AES, Apathy Evaluation Scale; ETOC, European Test of Olfactory Capabilities; FVT, Free-Viewing Task; MRI, Magnetic Resonance Imagery; TMS, Transcranial Magnetic Stimulation.

### 2.6 Sample size

#### 2.6.1 Patients with MDD

The sample size was estimated using EasyMed online software (https://easymedstat.fr), with an a priori power analysis based on a comparison of two binomial proportions (approximation of arscin).

We expect an approximately twofold increase in the remission rate for the iTBS combined with olfactory training group, compared to the iTBS alone group. This expectation is based on results from similar protocols using dual activation of the same neural network, such as the combination of high-frequency rTMS and visual smoking cues in individuals with tobacco use disorder, which reported 1.8-fold higher remission rate in the combination group than in the rTMS group alone (Dinur-Klein et al., 2014), and deep TMS with exposure in patients with post-traumatic stress disorder (Isserles et al., 2013), which reported a 3.5-fold higher response rate in the combination group than in the rTMS alone group.

Based on previous studies investigating the clinical efficacy of rTMS in treatment-resistant depression in both RCTs (Vida et al., 2023) and naturalistic settings (Bouaziz et al., 2023), we predict an approximate remission rate of 30% for the iTBS alone group. Thus, the expected remission rate for the iTBS combined with olfactory training group is estimated to be 60%. With a chi-squared test, an α risk of 5%, and a ß-power of 80%, a total of 74 MDD patients (37 per group) are required to be included.

As all patients enrolled in this trial will receive active treatment, we anticipate a low attrition rate (7%) and therefore plan to recruit a total of 80 patients with MDD (40 per group).

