##### 4.4.1.2 Clinical data analysis

The proportion of remissions and responses will be investigated using chi-squared tests or Fisher's exact test. Changes in scores of depression severity, anhedonia and olfactory capabilities over the study period within the two groups will be analyzed using a mixed 2-way repeated measures ANOVA (GROUP^*^TIME) or a generalized linear mixed model depending on the distribution of the data. Pearson correlations will be performed to examine the relationship between olfactory anhedonia and pre-treatment physical and social anhedonia, as well as the relationship between childhood trauma severity and response to treatment, the relationship between childhood trauma severity and anhedonia (physical, social, and olfactory), and the relationship between childhood trauma severity and depression severity. Type of medication and type of depression (unipolar vs. bipolar) will be included in the analysis. We did not expect differences in response between patients with unipolar and bipolar depression.

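### 37 patients per group gives about 75% power for 30% vs 60% remission, not the stated 80%; the plan's own method needs 42 per group

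*Protocol article*

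**What the plan says.** Section 2.6.1 sets out the whole calculation. The method is an "a priori power analysis based on a comparison of two binomial proportions (approximation of arscin"). For the control arm, "we predict an approximate remission rate of 30% for the iTBS alone group"; for the experimental arm, "the expected remission rate for the iTBS combined with olfactory training group is estimated to be 60"%. The test is chi-squared, alpha is 5% (sidedness not stated) and power is 80%. The conclusion is that "a total of 74 MDD patients (37 per group) are required to be included". Allowing for 7% attrition, the investigators "plan to recruit a total of 80 patients with MDD (40 per group").

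Three other places bear on the figure:
- Section 4.4.1.2 gives the analysis of the endpoint: "The proportion of remissions and responses will be investigated using chi-squared tests", with Fisher's exact test as the alternative.
- Section 4.4.2 keeps in the analysis only patients with a pre-treatment and at least one post-treatment evaluation.
- Section 5.1.2 sets significance levels of 0.005 at the interim and 0.048 at the final analysis.

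**The concern.** Every input is printed, so the sample size can be recomputed without any outside source, and 37 per group is too small for what is claimed. The statement concerns the primary endpoint. If the trial ends without a significant difference, readers will judge that result against a claimed 80% power that the design does not have. The assumed effect, a 30-point difference in remission, is already large, so there is little slack to absorb a shortfall.

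**Working it through.** **Inputs** (section 2.6.1 unless noted): p1 = 0.30; p2 = 0.60; alpha = 0.05, taken as two-sided because a chi-squared test of two proportions is two-sided in effect; power = 0.80; 1:1 allocation (section 3.1); attrition 7%.

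**Effect size on the arcsine scale.**
h = 2·asin(√0.60) − 2·asin(√0.30) = 1.7722 − 1.1593 = 0.6129, so h² = 0.3756.

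**Sample size by the plan's own method.**
n per group = 2(z₀.₉₇₅ + z₀.₈₀)² / h² = 2(1.960 + 0.8416)² / 0.3756 = 41.8, so 42 per group and 84 in total. The plan states 37 and 74. Its figure does not reproduce.

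**Could another formula explain 37?** Patients per group for 80% power:

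| Formula | Two-sided 5% | One-sided 5% |
|---|---|---|
| Arcsine | 42 | 33 |
| Pooled normal | 42 | 33 |
| Pooled, continuity-corrected | 49 | 40 |
| Unpooled normal | 40 | 31 |

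None gives 37. The arcsine formula at 75% two-sided power does: 2(1.960 + 0.6745)² / 0.3756 = 36.95, so 37. The match suggests that 75% was entered in the software, but the document does not show this.

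**Attrition step.** 74 / 0.93 = 79.6, so 80. This step is correct.

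**Power actually available.** By arcsine, power = Φ(h·√(n/2) − 1.960).
- n = 37: Φ(2.636 − 1.960) = 75.1%.
- n = 40: Φ(2.741 − 1.960) = 78.3%.

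Results by all methods at the 0.05 level, with the last two rows from enumeration of all possible tables:

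| Method | 37 per group | 40 per group |
|---|---|---|
| Arcsine | 75.1% | 78.3% |
| Pooled normal | 74.7% | 78.0% |
| Unpooled normal | 77.6% | 80.7% |
| Exact, uncorrected chi-squared | 74.2% | 79.6% |
| Exact, Fisher's test | 66.0% | 72.5% |

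**Effect of the 0.048 final level.** Arcsine power falls from 75.1% to 74.5% at 37 per group, and from 78.3% to 77.7% at 40. The exact chi-squared power does not change at either size (74.2% and 79.6%).

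**If dropouts counted as non-remitters.** This is not the plan's rule and is shown only as a sensitivity check. The rates become 0.93 × 60% = 55.8% and 0.93 × 30% = 27.9%. With 40 per group, arcsine power is about 73%.

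**The case against.** The strongest reply is that the practical shortfall is smaller than the headline. Eighty patients are recruited, and 40 evaluable per group gives 79.6% by exact chi-squared, close to 80%. The primary endpoint is read at the end of a two-week treatment, while follow-up runs to week 14. If some of the 7% attrition falls after the primary assessment, which section 2.6.1 does not say, the evaluable number lies between 37 and 40 per group and exact power between about 74% and 80%. That range is fair and belongs in the corrected text. It does not rescue the sentence, because section 2.6.1 presents 37 as the number required for 80% and the other six patients as replacements for losses.

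The rates are also stated as approximate: 30% vs 62% needs 36.7 per group and 28% vs 60% needs 36.4. This shows how sensitive the number is, but the plan commits to 30% and 60%, and moving a rate to fit the sample would be working backwards.

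Two side points deserve little weight:
- **Fisher's test.** The option is usually read as a fallback for small expected counts. Under the planned rates (pooled 45%) the smallest expected count at 37 per group is 37 × 0.45 = 16.65, so the fallback would not normally apply. The 66.0% holds only if Fisher's test were chosen anyway.
- **The 0.048 level.** It costs at most 0.6 points.

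**Conclusion.** The stated sample size is wrong on the plan's own inputs and method. At 37 evaluable patients per group the power is about 75% (75.1% arcsine, 74.2% exact chi-squared), roughly five points below the claim. The number required for 80% is understated by 84 − 74 = 10 patients. The probability of missing the assumed effect is about 25%, against the 20% implied. With all 80 patients evaluable, power is 78.3% by the plan's method and 79.6% by exact chi-squared. Only the unpooled normal approximation passes 80% there, and it is not the method named.

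The conclusion assumes a two-sided test and the stated rates of 30% and 60%. A one-sided 5% test would have about 84% power at 37 per group, but it is not stated, and it would have led to 33 per group. The conclusion does not depend on Fisher's test, the 0.048 level or the handling of dropouts.

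**What to change.** Keep 80 patients and correct section 2.6.1. State that, for 30% vs 60% with a two-sided chi-squared test, the arcsine approximation gives about 75% power with 74 evaluable patients and about 78% if all 80 are evaluable (74.5% and 77.7% at the 0.048 final level). State that the test is two-sided. It would also help to say in section 4.4.1.2 that the uncorrected chi-squared test is the primary test and that Fisher's test applies only if expected counts are small. That is a clarification, and the correction does not depend on it.

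The cost is wording only: no change to patients, endpoint or analysis, and a slightly less favourable stated power.

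If the sponsor wants a true 80% at the 0.05 level, the same arithmetic gives 42 evaluable per group. With 7% attrition that is 42 / 0.93 = 45.2, so 46 per group or 92 recruited, 12 more than planned.

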#### 2.6.2 Healthy volunteers

In order to provide evidence of impaired effective connectivity during odors perception in patients with major depressive disorder (MDD) compared to participants without a psychiatric disorder, a total of 40 healthy volunteers will be included in the study.

The final sample of the study will consist of 120 participants: 40 patients with MDD in the iTBS alone group, 40 patients with MDD in the iTBS combined with olfactory training group and 40 healthy volunteers.

### 2.7 Recruitment

#### 2.7.1 Patients with MDD

Patients will be recruited from specialized units for treatment-resistant depression and bipolar disorder at Le Vinatier, psychiatric hospital (Regional Expert centers). These units provide consultation to a large number of patients, from which the patients will be recruited. In addition, several recruitment strategies will be used, including flyers/brochures/posters, emails and websites/social media pages dedicated to patient recruitment in relation with the URPS Laboratoire participatif, AURA region.

#### 2.7.2 Healthy volunteers

To recruit the healthy controls, several calls for participation will be relayed by: posters in public places, publications on social network and websites, emails send to specific diffusion lists.

## 3 Methods: assignment of intervention

### 3.1 Sequence generation

Patients will be randomly assigned (1:1) to receive either iTBS alone or iTBS combined with pleasant olfactory stimulation. Computer-generated random numbers using the Sealed Envelope platform (https://www.sealedenvelope.com) will be used to generate the allocation sequence. Block of 2, 4, and 6 will be used to stratified the randomization.

### 3.2 Allocation concealment mechanism

The allocation sequence will be handled by an independent person from the Administrative Department of the Hospital to ensure that it is not disclosed to those responsible for enrolling and allocating patients.

### 3.3 Implementation

All the included participants will be assigned to a unique anonymous identification code, consisting of the group assignment number, the inclusion number and the patient's initials (first letter of last name and first letter of the first name). The person providing care will then administer the appropriate treatment associated with the inclusion number, according to the order of assignment.

### 3.4 Blinding

To ensure that patients are blinded to the allocated treatment, the information notice distributed to patients will state that odorants will be diffused during the TMS sessions, but at either a supraliminal or subliminal concentration, meaning that it may be normal not to smell anything. In addition, both the clinicians who complete the clinical scales and the researchers who analyze the data will be blinded to the allocation.

## 4 Methods: data collection, management, and analysis

### 4.1 Data collection methods

#### 4.1.1 Plans for assessment and collection of outcomes

The clinician-rated questionnaires will be scored by experienced psychiatrists who have undergone training to ensure homogeneity of scoring across raters. It is noteworthy that these scales are commonly used in research in the field of depression, and that all the psychiatrist-raters are experts in the treatment of depression.

### 4.2 Description of clinical scales and assessment tools

#### 4.2.1 Clinical assessments

##### 4.2.1.1 Symptoms severity

The MADRS is a clinician-rated questionnaire designed to assess the depression severity through 10 items. Each item has six levels of severity. Depression severity is also measured by a self-rated questionnaire, the 13-item BDI, in which participants will rate each item on a severity scale from 0 to 3. Manic states severity will be assessed with the 11-item YMRS. The total score can range from 0 to 60 (with 7 items rated 0 to 4, and 4 items rated 0 to 8).

##### 4.2.1.2 Early life adversity

Childhood trauma and maltreatment negatively affect rTMS-left DLPFC treatment outcome in patients with MDD (Hu et al., 2021). Therefore, the short form of the CTQ will be used, which includes 28 items, rated from 0 to 5 according to the occurrence of the event experienced. It allows to identify 5 different types of trauma: emotional neglect, physical neglect, emotional abuse, physical abuse, and sexual abuse. Subtotals can be calculated for each type of trauma to provide a nuanced understanding of the participant's childhood trauma experiences.

##### 4.2.1.3 Anhedonia

Physical and social anhedonia will be assessed using the Chapman Social Anhedonia Scale (SAS) and the Chapman Physical Anhedonia Scale (PAS). The SAS is a 40-item dichotomously scored self-report questionnaire measuring social anhedonia which reflects a preference for solitary activities. Scores can range from 0 to 40, with higher scores indicating a reduced ability to experience pleasure from social and interpersonal experiences. The PAS is a 61-item dichotomously scored self-report questionnaire that measures physical anhedonia which refers to the inability to experience pleasures from stimuli such as food, touch, smell, sex, temperature, movement, sound and physical sensations. Scores range from 0 to 61, with higher scores indicating a reduced pleasure from physical stimuli.

The second assessment tool is the SHAPS, a 14-item self-report questionnaire. Participants rate their agreement with statements using “strongly disagree,” “disagree,” “agree,” or “strongly agree.” Scores range from 0 to 14, with higher scores indicating greater levels of anhedonia.

##### 4.2.1.4 Apathy

The Apathy Evaluation Scale (AES) has been developed to quantify and characterize apathy in adults. The scale consists of 18 items assessing the emotional, cognitive and behavioral aspects of apathy in the month prior to the assessment. The rating is based on a 4-point Likert scale, with 1 corresponding to “not at all true” and 4 corresponding to “very true.” The version used in this study is the one completed by the participants themselves (AES-S).

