#### 1.2.2 Secondary objectives

##### 1.2.2.1 Clinical outcomes

We will assess the acute and long-term effects of the treatment on several clinical features of MDD: remission (MADRS_10_ < 10) and response (reduction of at least 50% in MADRS_10_ score), severity of self-rated depression (BDI_13_), physical and social anhedonia and apathy immediately after the treatment, after 1-month and 3-month follow-up.

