### 2.3 Intervention

All stimulations for therapeutic intervention will be delivered using a MagPro X100 (MagVenture, Mag2Health, France) equipped with a 65 mm figure-of-eight coil with active cooling (MCF-Cool B65). Patients will be comfortably installed in a dedicated room for brain stimulation. During each session, the 3D T1-weighted images of all participants will be used for neuronavigation and the position and orientation of the coil will be monitored using a neuronavigation system (Syneika system, France).

At the first session, the primary motor cortex (M1) hand area will be located by identifying the optimal scalp sit (hotspot) that elicits the largest amplitude of motor evoked potentials (MEPs) in the right hand's first dorsal interosseus (FDI) muscle for a given intensity. The resting motor threshold (rMT) will then be established as the lowest stimulation intensity to evoke at least 5 MEP of 50 μV peak-to-peak amplitude from 10 consecutive (Rossini et al., 1994).

For the rTMS protocol, the coil will be positioned over the left DLPFC based on the individual anatomical T1-weighted MRI. The targeted left DLPFC will be identified based on a predefined identification by the Syneika neuronavigation system, i.e., the junction between areas BA9 and BA46, according to the algorithm proposed by Mylius et al. (2013). The exact same target will be maintained for each rTMS session to ensure precise and reproducible placement of the stimulation coil.

The rTMS protocol includes 50 sessions over 10 days (i.e., 5 sessions per working day, 1 h apart, for 2 weeks). Each session lasts 9min40 and involves 1,800 pulses at 90% rMT, delivered in bursts of 3 pulses at 50 Hz, repeated at 200 ms intervals for 2 s (i.e., at 5 Hz). This particular rTMS protocol is called intermittent theta-burst stimulation (iTBS). A 2-second train of iTBS is repeated every 10 s (Cole et al., 2022).

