#### 2.4.2 Other clinical and behavioral outcomes

Several clinical and behavioral features will be assessed using:

- the 10-item MADRS total scores to assess depression severity.- the number of responders, defined as those who show a reduction of at least 50% in their MADRS score.- the 13-item Beck Depression Inventory (BDI) (Gould, 1982), to assess self-rated depression.- the 11-item Young Mania Rating Scale (YMRS) (Young et al., 1978), to assess manic states.- the Childhood Trauma Questionnaire (CTQ) (Bernstein et al., 2003) to study early life adversity.- the Chapman Social Anhedonia Scale and the Chapman Physical Anhedonia Scale (Chapman et al., 1976) to investigate respectively physical and social anhedonia.- the Snaith-Hamilton Pleasure Scale (SHAPS) (Snaith et al., 1995) to assess global anhedonia.- the Apathy Evaluation Scale (AES) (Marin et al., 1991) to assess apathy.- the Free-Viewing task (FVT) to assess cognitive biases, more precisely, early and sustained emotional attentional biases.

These outcomes will be assessed before and after the 50 iTBS sessions. The same outcomes will also be assessed at 1 and 3 months after treatment and compared between the two groups. In addition, the relationship between early life adversity and depression severity will be examined, as well as its association with the evolution of depressive symptoms and especially anhedonia.

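### The week-2 apathy rating looks back one month over a two-week course, so half or more of what it rates precedes treatment and an acute effect would be attenuated

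*Protocol article*

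**What the plan says.** Section 4.2.1.4 gives the recall period of the AES: "The scale consists of 18 items assessing the emotional, cognitive and behavioral aspects of apathy in the month prior to the assessment". It adds that patients complete the scale themselves. No shorter recall is stated for any visit.

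On treatment length, section 2.3 says: "The rTMS protocol includes 50 sessions over 10 days", which it explains as five sessions per working day for two weeks.

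On timing, section 1.2.2.1 lists among the acute and long-term objectives "physical and social anhedonia and apathy immediately after the treatment, after 1-month and 3-month follow-up". Section 2.4.2 includes the AES in its list and says "These outcomes will be assessed before and after the 50 iTBS sessions", then "The same outcomes will also be assessed at 1 and 3 months after treatment and compared between the two groups".

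Table 1 differs. For patients it marks the AES at week 0 and week 2 only. The week-6 and week-14 visits exist and carry the MADRS, BDI, Chapman scales and SHAPS, but have no AES mark.

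**The concern.** A one-month look-back taken at the end of a two-week course must reach back before the first session. The week-2 score then mixes untreated and treated days, and part of its window is the same stretch of time that the baseline AES already rated. Any effect of adding odorants is pulled towards zero at that visit.

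The practical risk is a false negative. A week-2 comparison with no difference could be reported as showing that odorants do nothing for apathy, when the questionnaire asked largely about days before treatment. If Table 1 governs, no later AES exists to correct that reading, and no analysis can recover the information afterwards.

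**Working it through.** The plan states no figure for the AES, so there is none to reproduce.

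**Inputs**
- Recall window M: one month (4.2.1.4), taken as 28, 30 or 31 days.
- Treated span T, first session to rating: 10 working days over two weeks (2.3). This is 12 calendar days if both weeks run Monday to Friday, or 14 if treatment fills the gap between the week-0 and week-2 ratings in Table 1.
- 40 patients per arm (2.6.1) and alpha 0.05 (4.4.1), taken as two-sided.

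**Share of the window before treatment**, (M − T)/M:

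| M | T = 12 | T = 14 |
|---|---|---|
| 28 | 16/28 = 57% | 14/28 = 50% |
| 30 | 18/30 = 60% | 16/30 = 53% |
| 31 | 19/31 = 61% | 17/31 = 55% |

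**Overlap with the baseline window.** With ratings 14 days apart the two windows share M − 14 = 14, 16 or 17 days. If the baseline rating falls just before a 12-day course, they share M − 12 = 16, 18 or 19 days.

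**Share of a true effect that would show**, assuming every day counts equally:
- Full effect from day 1: T/M, from 12/31 = 39% to 14/28 = 50%.
- Linear build-up to the last session: the mean effect over treated days is half the final one, so T/(2M), from 19% to 25%.

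**Sensitivity to equal weighting.** Suppose treated days counted double (an assumption). With M = 30 and T = 12 the visible share of an immediate effect is 2 × 12/(2 × 12 + 18) = 24/42 = 57%, against 40% with equal weights. The more recent days dominate, the smaller the loss.

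**What this does to power.** Illustration only: the effect size d (in SD units) is assumed, the SD is unchanged by dilution, and f is the visible share. Power ≈ Φ(d × f × √(40/2) − 1.96).
- d = 0.63, f = 1: Φ(2.82 − 1.96) = 80%
- d = 0.63, f = 0.50: Φ(1.41 − 1.96) = 29%
- d = 0.63, f = 0.40: Φ(1.13 − 1.96) = 20%

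**Week 6.** Counting back 28 days from week 6 reaches week 2. With 30 or 31 days the window takes in the last 2 or 3 days before the week-2 visit, but none before the first session. The pre-treatment share is 0%.

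**The case against.** A reader might infer that the acute apathy objective cannot be answered, or that the week-2 score has no meaning. The documents do not support that. Section 3.1 says "Patients will be randomly assigned (1:1) to receive either iTBS alone or iTBS combined with pleasant olfactory stimulation", so both arms carry the same pre-treatment share. The comparison between arms is not distorted under the null, and a difference found at week 2 would still count. The loss is of sensitivity.

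It is also fair to say that the size of the loss is not known. Nothing in section 4.2.1.4 tells us how patients combine days within the month. If they answer mainly from how they feel now, the attenuation is modest. This objection stands, and the percentages above should be read with it in mind.

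Two further points stand. Section 4.4.1.2 does not name apathy among the scores for its group-by-time models, so the concern attaches to any week-2 comparison of the arms and not to a specified model. And apathy is one of many secondary measures: remission on the MADRS, the sample size and the interim stopping rule do not depend on it.

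What does not stand is the idea that the mismatch might be settled elsewhere. Recall period, course length and visit timing are all given, and section 7.3 presents the article as the full protocol.

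**Conclusion.** The point holds as a loss of sensitivity. Between 50% and 61% of the week-2 AES window precedes treatment, and the window overlaps the baseline one by about two weeks or more. That follows directly from the stated recall and course length. Under equal weighting of days, roughly 40 to 50% of an immediate effect, or roughly 20 to 25% of a linearly growing one, would be visible. Less is lost if recent days weigh more. A null at week 2 is weakly informative, while a positive finding remains credible. The matter is worth correcting because on Table 1 this diluted rating is the only post-treatment apathy measure. It does not justify dropping the acute objective.

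**What to change.** 1. Reconcile Table 1 with sections 1.2.2.1 and 2.4.2 by marking the AES for patients at week 6 and week 14.
2. Name week 6 as the main apathy time point, since no part of its recall window precedes treatment.
3. Keep week 2 as a secondary reading, and state that its recall window includes time before treatment and that a null there is not evidence of no effect.
4. Report the week-6 comparison on observed values beside the LOCF analysis of section 4.4.2. For a patient who leaves after week 2, LOCF would put the diluted week-2 score in the week-6 cell.

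**Cost.** If the text governs, only Table 1 and some wording change. If Table 1 governs, one short self-rated questionnaire is added to each of two follow-up visits that already take place. The downside is that apathy is read mainly at one month and not at the end of the course.
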